#### Inflammatory and neurohormone biomarker assays

We have selected a panel of biomarkers based on our pilot study of neuroinflammation in early psychosis funded by an R21 from NIMH. Biomarkers will be assayed in the UCSD Clinical Research Biomarker Laboratory of [name] [name]. Morning blood samples will be drawn and following centrifugation and separation, and plasma or serum will be stored at − 80 °C until assays are conducted. Levels of inflammatory biomarkers will determined in duplicate using mesoscale assays for biomarkers with internal controls (Meso Scale Discovery, Rockville, MD). The biomarkers include pro-inflammatory cytokines, chemokines, markers of vascular injury (C-reactive protein [102], vascular endothelial growth factor), and neural plasticity (BDNF).

We will utilize procedures for saliva collection and cortisol assay used in our previous studies [47]. Three saliva samples will be obtained at hourly intervals in the morning of each assessment. Sample numbers and collection time will be noted and stored at − 20 °C until assay. Participants will be given instructions regarding food and activity restrictions. For the salivary cortisol assay, the Salimetrics (Salimetrics, LLC, College Park, PA) High Sensitivity Salivary Cortisol Enzyme Immunoassay Kit is used. This assay captures the full range of salivary cortisol levels (0.003 to 3.0 μg/dL) requiring only 25 µL of saliva per test. Samples are assayed in duplicate.

#### Eating behavior and metabolic profile

Eating behavior will be assessed with the Dutch Eating Behaviors Questionnaire, Three-Factor Eating Questionnaire, and Food Diary. The metabolic profile will be assessed with anthropomorphic measurements (height, weight, basic metabolic index [BMI]) and plasma metabolic measures (insulin, glucose, HgA1C, lipids).

#### Neurophysiological methods

Neurophysiological markers can provide corroborative data for treatment-related changes in underlying brain chemistry and associated changes in clinical symptoms of psychosis. The following evaluations will be conducted at baseline and at the end of the study.

In the startle prepulse inhibition (PPI) paradigm [103], electrodes (Ag/AgCl) are placed below and at the outer canthus of each eye. A customized startle-stimulus generating program (Grace Design Model m902 Amplifier and Neurobehavioral Systems Presentation software) will be used. The startle stimuli will be presented binaurally through headphones (TDH-39P) and include 70 dB [A] broadband background noise with a pulse (115 dB [A], 40-ms noise burst) presented either alone or following (30, 60, or 120 ms) a prepulse (86 dB [A], 20-ms noise burst). EMG activity will be analyzed using Brain Vision Analyzer (Cortech Solutions, Wilmington, NC) and high-pass filtered at 28 Hz at 12 dB/Oct. The waveform is then smoothed using a 40-Hz 24 dB/Oct low-pass filter. The magnitude of the peak startle response (highest point between 30 and 100 ms) is determined. Subjects with a relative lack of startle-elicited eye blink are excluded. The outcome is PPI or the percentage of change in startle magnitude to prepulse + pulse versus pulse-alone trials.

Stimulation, recording, and analysis techniques for calculating MMN amplitude will follow established methods [104, 105]. Participants will be presented with binaural tones (1 kHz computer-generated square wave stimuli, 85 dB[A] SPL, 1 ms rise/fall) with a fixed stimulus onset-to-onset asynchrony of 500 ms. Standard (*P* = 0.90; 50 ms duration) and deviant (*P* = 0.10; 100 ms duration) tones will be presented to participants in pseudorandom order while they watch a silent video. MMN waveforms will be generated by subtracting event-related potential (ERP) waveforms in response to standard tones from the ERPs generated in response to the deviant tones. The MMN amplitude will be measured as the mean voltage from 135 to 205 ms. The primary dependent measure is MMN amplitude at electrode Fz.

#### Safety and other assessments

All participants will receive frequent health check-in appointments as part of the study. These will occur at baseline, after 1 week after initiating treatment, and then at 4 and 8 weeks. Assessments included in this visit are intended to screen for adverse events that have been described in past studies of CBD notably sedation and GI effects as above, as well as any other adverse events not previously reported. Vital signs will provide information about any possible elevations in temperature, or changes in heart rate or blood pressure. Blood samples will be collected to ensure that there are no adverse effects of the drug in terms of renal and hepatic functioning. In the case that any adverse event is reported, the investigator will assess its severity and relationship to the drug. They will determine how to proceed with treatment. It may include stopping treatment altogether if that is warranted. Detailed documentation will be kept of any and all adverse events. All participants will be given contact information to reach the principal investigator and study staff. This will include a number that can be reached 24/7 in case of emergency. It is possible that early psychosis patients will develop worsening symptoms and require emergency treatment or a higher level of care. In these situations, we will offer alternate treatments that will be consistent with the standard of care in the community. Individuals will be referred to the appropriate resource based on their insurance funding and acuity of the problem. Discontinuation from study intervention may occur if the patient is noncompliant with the treatment or fails multiple (more than 3) follow-up appointments and does not reschedule. Participant satisfaction will be assessed with an exit survey regarding the overall satisfaction with the trial including the tolerability.

### Data analysis

Power analyses were conducted allowing for a 20% dropout rate, and a sample size of 120 early psychosis patients (60 per group), measured at 3 time points, was calculated as sufficient to detect a treatment difference in PANSS/CGI total score, biomarker assessments, food intake and metabolic indices, and neurophysiological measures between CBD and placebo on the change from baseline to end of treatment, with a two-tailed 1% significance level and 80% power. We selected a sample size that provided a minimum of 80% power for medium effect sizes based on the anti-inflammatory outcome measures reported in multiple studies [106–108] that show medium effect sizes (Cohen *d* = 0.47; Hedges *g* =  − 0.39 in EP) for clinical symptoms.

Ensuring adequate recruitment requires a number of strategies, including providing announcements to local primary care practitioners, including community pediatricians, family practice physicians, educators, clinical social workers, psychologists, and psychiatrists. Ads are also posted on various social media platforms. Additionally, ResearchMatch.org and clinicaltrials.org will be utilized as a recruitment tool for this protocol. We estimate that we will be able to recruit five new patients every month based on past referrals.

Data will be analyzed using a mixed model [109] for all clinical, neurocognitive, biomarker, eating behavior, and electrophysiological markers. This method allows the inclusion of subjects with missing data or those who were terminated early in the study, without relying on data imputation procedures. This method provides an estimate of the individual variability around the population trend, the variability of the individual intercepts (baseline values) and slopes (changes across time), and the correlation between them. The model will include a random intercept, a random effect for assessment time, and fixed effects for comparison groups and group-by-time interaction. A fully saturated treatment-by-time model will be utilized for inference. Co-variance structure will be chosen based on Akaikes Information Criterion (AIC). Random group-level treatment effects will also be evaluated for importance based on the model AIC. Any group-level effects to be incorporated into the model. Denominator degree’s of freedom will be calculated using the Kenward-Roger small sample correction. Data will be analyzed from all randomized subjects on whom we have a baseline assessment and at least one post-baseline evaluation. Hypothesis 5 will be testing using the multiple regression procedure. All tests will be done using the SPSS version 24.

We will explore predictors (moderators) of treatment response including baseline symptom severity, neurocognition, biomarker (cortisol and inflammatory markers), and neurophysiological markers by building hierarchical linear models (HLM). The independent variables are the treatment group, moderator, and the treatment × moderator interaction. Mediation analyses will use a similar linear mixed models approach. Two conditions must be met: (1) correlation between the mediator and treatment and (2) relationship between the mediator and outcome. First, we will test the effect of the treatment group and the group × time interaction on the mediator, and we expect a statistically significant group × time interaction. Second, we will test the effects of mediator by group interaction on the outcome in the model that includes group and time; we expect a statistically significant mediator × time or mediator × group × time interaction.

Number, time, reasons, and grade (severity) of adverse events will be summarized overall and by treatment using mean (SD) or median (IQR), range, and *N* (%) as appropriate. The proportion of subjects with adverse events will be compared between treatments using the McNemar test. The number of adverse events will be compared between treatments using the Wilcoxon signed-rank test. Serious adverse events are reported to the IRB within 24 h of the occurrence of the event and follow the proper procedures regarding the reporting of expectedness, seriousness, severity, and causality. The study subjects are instructed to report any new unusual symptoms, suspected side effect, or health-related events as soon as they occur during the 7-week trial period. On the weeks where they do not have an in-person visit, the subjects are contacted by phone by the clinical psychologist and asked a series of questions to assess any side effects that they might be experiencing. All serious adverse events are also reported in the annual DSMB report.

Baseline demographic measures and relevant diagnostic characteristics will be summarized as described under general approach. If dropout occurs, the characteristics of participants who withdraw from the study prematurely will be compared to those who complete the study as described under general approach. We used the SPIRIT reporting guidelines for this manuscript [110].

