As outlined in the study design (Fig. 1) and SPIRIT (Fig. 2), the trial will include 120 patients in the early stages of psychosis who will be randomly assigned in a 1:1 ratio to receive 1000 mg of cannabidiol or matching placebo as an add-on to current treatment to in a 8-week double-blind superiority randomized controlled trial to be performed over 3 years. The unblinded study statistician has created a list of participant identification numbers with randomized treatment assignments using the SPSS software prior to the start of the study subject recruitment. Blocked randomization will be used with a random block size (4 or 6). Subjects will be randomized to the study treatment group in a 1:1 ratio. No stratification method will be used. A research associate on the team who is not part of the study will be provided with that subject’s randomization code. Any violations of the inclusion and exclusion criteria, reasons for randomization failure including major protocol deviation, lost to follow-up, voluntary withdrawal, and study termination, will be communicated to the study statistician. This research associate is also the only person who is not blinded and who has access to the list that identifies the unique numbers on the relabeled bottles of the two products. They are then responsible for assigning the bottles to the patient. All clinical staff and participants involved in the study will be blinded with the sole exception of the independent statistician. The design is sufficiently powered to answer questions about the efficacy of CBD as an augmentation to antipsychotics in EP, predictors, mediators, and moderators of treatment response and further our understanding of the mechanism of action of CBD in early psychosis. Symptoms, eating behaviors, metabolic parameters, and hormonal and neuroimmune marker levels will be evaluated at baseline, 3 weeks, and 8 weeks, and neurocognitive and neurophysiologic assessment will be performed at baseline and 7 weeks. We will work closely with the UCSD Center for Medicinal Cannabis which has performed multiple CBD trials. UCSD IRB approval, FDA IND approval, and ClinicalTrials.gov registration are in place. Data will be deidentified and stored in RedCAP, a secure dataset available through UCSD. A data monitoring committee is made up of members of both funding agencies, which has assisted in the development of the database and ensuring compatibility with data forms. There is a Data and Safety Monitoring Board (DSMB) that reviews the progress of the study, recruitment, dropouts, and adverse events of trial participants on an annual basis, the board is made up of an independent group of investigators. Any protocol modifications will be reported to IRB, trial registry, and DSMB.

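### The stated inputs do not give 80% power at a two-tailed 1% level: power is about 38–48% for d = 0.47 and 24–32% for g = 0.39 if these are in SDs of change

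*Protocol article*

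**What the plan says.** The sample-size paragraph under Data analysis fixes every main input. The calculation allows for attrition ("Power analyses were conducted allowing for a 20% dropout rate"). It rests on "a sample size of 120 early psychosis patients (60 per group), measured at 3 time points" and is made "with a two-tailed 1% significance level and 80% power". The contrast is CBD against placebo on the change from baseline to end of treatment. It is claimed for the PANSS/CGI total score, biomarkers, food intake and metabolic indices, and neurophysiological measures. The power claim is "We selected a sample size that provided a minimum of 80% power for medium effect sizes based on the anti-inflammatory outcome measures", and the medium effects given are a Cohen d of 0.47 and a Hedges g of −0.39, the latter "0.39 in EP) for clinical symptoms". No SD, SD scale or within-subject correlation is given.

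Overall design widens the claim: "The design is sufficiently powered to answer questions about the efficacy of CBD as an augmentation to antipsychotics in EP, predictors, mediators, and moderators". No interaction or mediation effect size is given there or under Data analysis.

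**The concern.** An effect of 0.47 SD or less needs a large trial at a 1% level, and 48 to 60 patients per arm looks too few for 80% power on a two-group comparison. This is the only sample-size justification in the article. If it is wrong, a null result will be read as coming from a trial that had at least an 80% chance of finding the assumed effect, when the chance may have been below one half. Null predictor, mediator and moderator results would be over-read in the same way.

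The calculation also leans on three time points for measures that do not have three.

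**Working it through.** **Inputs (Data analysis and Overall design).** Two-sided alpha 0.01; 60 randomised per arm, 1:1; 20% dropout, so 60 × 0.8 = 48 completers per arm; effects 0.47 and 0.39; contrast is the difference in change to end of treatment.

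**Step 1. Effects in SDs of change.** The test is a two-sample comparison with df = 2n − 2 and noncentrality δ = d·√(n/2). Power is the noncentral-t probability beyond the two-sided 1% critical value.

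| n per arm | critical t | δ (0.47) | power (0.47) | δ (0.39) | power (0.39) | detectable at 80% |
|---|---|---|---|---|---|---|
| 48 | 2.629 | 2.303 | 37.7% | 1.911 | 24.2% | 0.710 SD |
| 60 | 2.618 | 2.574 | 48.5% | 2.136 | 31.9% | 0.633 SD |

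The stated 80% is not reproduced.

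**Step 2. Could a different reading recover 80%?**
- Rounding up to d = 0.50 with no dropout at all gives 55%.
- Relaxing to two-sided 5% gives 63% and 47% with 48 per arm, and 72% and 56% with 60 per arm.
- One-sided 1% with d = 0.47 gives 48% (48 per arm) or 59% (60 per arm).
- About 80% appears only at one-sided 5% (82% for d = 0.47 with no dropout), which contradicts the stated level.

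**Step 3. Sample size the claim would need at two-sided 1%.** d = 0.47 needs 108 evaluable per arm, and 216/0.8 = 270 randomised. g = 0.39 needs 156 per arm, and 312/0.8 = 390 randomised.

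**Step 4. Effects in raw-score SDs.** Let ρ be the baseline-to-end correlation. The variance of the contrast is multiplied by 2(1 − ρ) for a change score, or by 1 − ρ² with baseline adjustment. Setting the rescaled effect equal to the detectable effect m from Step 1 gives ρ = 1 − (d/m)²/2 for a change score and ρ = √(1 − (d/m)²) with baseline adjustment.

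| | (d/m)² | ρ, change score | ρ, baseline-adjusted |
|---|---|---|---|
| 0.47, n = 48 | 0.438 | 0.78 | 0.75 |
| 0.47, n = 60 | 0.552 | 0.72 | 0.67 |
| 0.39, n = 48 | 0.302 | 0.85 | 0.84 |
| 0.39, n = 60 | 0.380 | 0.81 | 0.79 |

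At ρ = 0.5 the change-score factor is 2(1 − 0.5) = 1, so the Step 1 figures apply unchanged. Baseline adjustment at ρ = 0.5 with 48 per arm gives 51% and 34%.

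**Step 5. Number of assessments.** The power sentence lists neurophysiological measures among outcomes measured at three time points. Overall design places neurocognitive and neurophysiologic assessment at baseline and 7 weeks only. Neurophysiological methods says baseline and end of study. Both give two assessments.

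**Step 6. Predictors, mediators and moderators.** Overall design says the trial is adequately powered for these. Data analysis says that predictors (moderators) will be explored, and the Discussion says that moderators and mediators will be explored. With no effect size stated, no power can be computed from the article.

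**The case against.** The strongest defence is that the article describes a repeated-measures design analysed with a mixed model, and the power of such a design depends on a within-subject correlation and on the SD scale of the effect. A journal article may leave both to the full protocol, and the studies behind the two effect sizes are not at hand. This stands as a limit on certainty: a reader might infer that the trial's true power is 38%, and the documents do not support so flat a statement. It does not restore the claim. For the contrast that the article names, the correlation would have to be high, and for g = 0.39 at least about 0.79 even with no dropout. Averaging both post-baseline visits with baseline adjustment would give 75% to 81% for d = 0.47 at correlations of 0.5 to 0.6 (48 per arm, normal approximation). That is a different contrast, and g = 0.39 still reaches only 55% to 62%. For neurophysiology there is no intermediate visit to average.

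A second defence is that 48 per arm is the low end, because the mixed model keeps anyone with a baseline and one later evaluation. This is right, and it is why the result is given as a range up to all 60 per arm.

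A reader might also infer that the moderator claim is impossible, since an interaction with an evenly split binary moderator has twice the standard error of the main effect. The article does not support that. The moderators it names (symptom severity, neurocognition, biomarkers, neurophysiology) are mainly continuous, and for a continuous moderator scaled per SD the interaction has about the same standard error as the main effect. Mediation power cannot be computed at all.

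**Conclusion.** The point holds in a conditional form: a minimum of 80% power is not supported by the inputs printed beside it. The Step 1 range rests on effects in SDs of change and a two-group comparison at end of treatment. The only escape for that contrast is raw-score scaling with a high correlation that the article does not state. It is hardest to reach for g = 0.39, the value that the article ties to early psychosis. The two-visit schedule for neurophysiology is a plain internal contradiction. For predictors, mediators and moderators, the conclusion is limited to this: the adequacy claim has no stated basis and conflicts with the article's own exploratory wording.

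**What to change.** Keep N at 120 and change the text as follows.

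1. Replace the power claim under Data analysis with wording such as:

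> With 96 evaluable patients the trial has 80% power at a two-sided 1% level for a difference of about 0.71 SD of change (0.63 SD if all 120 are evaluable). For effects in SDs of change, power is about 38% to 48% for d = 0.47 and 24% to 32% for g = 0.39.

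2. State the SD scale of the two cited effects. If a within-subject correlation is relied on, give its value and source and tabulate power over a range. For example, change-score power with 48 per arm at ρ = 0.5, 0.6, 0.7 and 0.8 is 38%, 48%, 64% and 84% for d = 0.47, and 24%, 32%, 44% and 65% for g = 0.39.
3. Correct the number of time points for neurophysiology to two and give its power on that basis.
4. In Overall design, remove the statement of adequate power for predictors, mediators and moderators and call these analyses exploratory, in line with Data analysis and the Discussion.

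The cost is a less favourable power statement. No patients, visits or design features change.

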### Participants

In order to be eligible to participate in this study, an individual must meet all of the following criteria:Between the ages of 16 and 30.Acceptable diagnoses will include attenuated psychosis syndrome (APS) per the Structured Interview for Prodromal States (SIPS) [79] or first-episode psychosis (onset within the last 2 years) and meet one of the following diagnoses: psychosis NOS, schizophreniform, schizophrenia, and schizoaffective per the Structured Clinical Interview for DSM-V [80].Stabilized on a current treatment regimen for at least 4 weeks prior to initiating the trial consistent with the FDA-NIMH-MATRICS guidelines for clinical trial design for clinical enhancing drugs [81]:Clinically stable and in a nonacute phase of their illness for at least 2 monthsIf currently on antipsychotics, will have been maintained on a current antipsychotic for at least 6 weeks, with no change in antipsychotic dose for the previous 4 weeksExhibit no more than moderate levels of positive symptoms (defined by ratings of ≤ 4) on PANSS items P1 (delusions), P2 (conceptual disorganization), P3 (hallucinatory behavior), P5 (grandiosity), P6 (suspiciousness), and G8 (unusual thought content), but still symptomatic (defined by ratings ≥ 2 on positive symptoms items); no more than a minimal level of depressive symptoms as assessed by the Calgary Depression Scale for Schizophrenia (CDSS) [82]

An individual who meets any of the following criteria will be excluded from participation in this study:Concomitant medical or neurological illnessSignificant head injuryCurrent substance misuseIQ < 80 (below which is considered at least borderline-impaired on Stanford-Binet Fifth Edtion)High suicidal risk assessed by the Columbia-Suicide Severity Rating Scale (C-SSRS) [83]Pregnant women and those who do not agree to avoid becoming pregnantPatients requiring treatment with azelastine, fluticasone, dronabinol, valproic acid, or divalproex sodium

If clinically significant, untreated symptoms are found to be present at baseline, or are found to develop during the course of the study, participants will be advised to consult with their mental health care provider and will also be provided with referrals to UCSD (e.g., UCSD CARE Early Psychosis Specialty Clinic-clinical arm of the CARE) and appropriate clinicians in the community. These participants will continue to be followed in the study, with information on treatment recorded in the database.

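### The mixed model gives each arm its own baseline mean, so the treatment contrast is an unadjusted change score: valid, but less precise than a baseline-adjusted contrast

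*Protocol article*

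**What the plan says.** The protocol article's Data analysis section sets out one mixed model for the clinical, neurocognitive, biomarker, eating-behaviour and electrophysiological outcomes, with random terms for intercept and time and "fixed effects for comparison groups and group-by-time interaction". It adds: "A fully saturated treatment-by-time model will be utilized for inference". The same paragraph says the method estimates "the variability of the individual intercepts (baseline values) and slopes (changes across time), and the correlation between them", so baseline is modelled as a response and is not a covariate. The sample-size paragraph of that section names the comparison as one "between CBD and placebo on the change from baseline to end of treatment".

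The Abstract names symptoms and neurocognition as the primary outcomes. Under Overall design, symptoms are measured at baseline, 3 weeks and 8 weeks, and neurocognition at baseline and 7 weeks. Baseline severity otherwise enters the analysis only as an exploratory moderator.

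**The concern.** A saturated treatment-by-time mean that includes the baseline visit lets the two arms have different baseline means. The group-by-time contrast then subtracts any chance baseline difference between the arms in full. Under randomisation the true difference is zero, and the efficient weight for the observed one is the regression slope of endpoint on baseline, which is usually below 1. Subtracting with weight 1 carries baseline noise into the treatment estimate. The random intercept does not change this: it models correlation within a patient but leaves the arm-specific baseline means free.

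Precision is at stake on both primary outcomes, and it can be recovered without another patient or another measurement.

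**Working it through.** **Inputs from the article.** 60 per arm, 20% dropout (48 per arm, 96 in all), two-sided 1% level, 80% power, and d = 0.47 (or g = 0.39 in early psychosis), all from Data analysis. The article gives neither a baseline-to-endpoint correlation nor SDs, so rho and the SD ratio below are assumptions.

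**The plan's own figure.** The article puts no number on this point. Its sample size does not supply rho directly either. With d = 0.47 standardised on the analysed variable, n = 2(2.576 + 0.842)²/0.47² = 106 per arm, or 133 after dividing by 0.8, for a total of 266 and not 120. That is a separate matter, but it gives one rough anchor. With 48 per arm, the difference detectable with 80% power is (2.576 + 0.842)·√(2/48) = 0.698 SD of the analysed variable. If d is instead in raw-score SDs, a change-score analysis reaches 0.698 when 0.47/√(2(1−rho)) = 0.698, so rho is about 0.77. For g = 0.39 the same step gives about 0.84.

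**Step 1: equal SDs.** Let sigma be the SD at each visit and n the number per arm.

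- Difference in mean change: variance (2/n)·2·sigma²·(1−rho).
- Baseline-adjusted difference: variance (2/n)·sigma²·(1−rho²).
- Ratio: 2(1−rho)/(1−rho²) = 2/(1+rho).

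| assumed rho | 2(1−rho) | 1−rho² | ratio | extra patients for equal precision |
|---|---|---|---|---|
| 0.3 | 1.40 | 0.91 | 1.54 | 54% |
| 0.5 | 1.00 | 0.75 | 1.33 | 33% |
| 0.6 | 0.80 | 0.64 | 1.25 | 25% |
| 0.7 | 0.60 | 0.51 | 1.18 | 18% |
| 0.8 | 0.40 | 0.36 | 1.11 | 11% |
| 0.9 | 0.20 | 0.19 | 1.05 | 5% |

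At rho 0.5, for example, the change-score contrast needs 96 × 1.333 = 128 evaluable patients to match the precision of an adjusted contrast with 96. At the anchor values the ratio is 2/1.77 = 1.13 and 2/1.84 = 1.09 (about 1.085 with unrounded rho), a loss of roughly 8 to 13%.

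**Step 2: does the stated model really behave this way?** Exact generalised least squares with three visits, compound symmetry, complete data and 48 per arm gives the saturated model a variance of 0.0417 at rho 0.5 (sigma = 1). This equals the change-score formula, 2·2·(1−0.5)/48. Its ratio to the model with a common baseline mean is 1.333, 1.250 and 1.176 at rho 0.5, 0.6 and 0.7, as in the table.

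**Step 3: unequal SDs.** Let k be the endpoint SD divided by the baseline SD. The ratio becomes (1 + k² − 2·rho·k)/(k²(1−rho²)).

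- k = 1.2: 1.24/1.08 = 1.15 at rho 0.5, and 0.76/0.734 = 1.03 at rho 0.7.
- k = 0.8: 0.84/0.48 = 1.75 at rho 0.5, and 0.52/0.326 = 1.59 at rho 0.7.

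**Step 4: direction.** The numerator minus the denominator is 1 − 2·rho·k + rho²k² = (1 − rho·k)², which is never negative. Apart from the degree of freedom spent, adjustment cannot lose precision, whatever rho and k are.

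**The case against.** The strongest reply is that nothing here is an error. The contrast is unbiased, its type I error is controlled, and it targets the comparison that the sample-size paragraph names. All of that stands. A reader might infer that the planned result would be biased or invalid, and the article does not support that inference.

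The size is also open. Patients must be clinically stable and are followed for only 8 weeks, so a rho above 0.7 cannot be excluded. Entry limits on PANSS positive items may compress the baseline spread, which would push k above 1 and the loss down towards 3 to 15% at rho 0.7 to 0.5. This stands too: 18 to 33% is one slice of the range, not a result of the trial's documents.

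A further reply is that a SAP may refine the model. That is fair for covariates in general, since the article's list is visibly abbreviated. It is weaker for baseline, because the article itself makes baseline a response and fixes a saturated mean for inference.

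Two stronger readings should be resisted.

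- That the missing terms for APS versus first-episode psychosis, or for antipsychotic use, are part of this loss, given "No stratification method will be used". None of the figures above comes from those terms. A change contrast already cancels constant level differences between such groups; only different trajectories would matter, and the article gives nothing to quantify them. Unstratified randomisation is a legitimate choice, and covariate lists are commonly left to a SAP.
- That a specific gain in power can be quoted. It would depend on rho and on whether d is in raw-score or change-score SDs, and the article states neither.

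**Conclusion.** The point holds as a loss of efficiency. As written, the model tests an unadjusted difference in change from baseline, and a baseline-adjusted contrast would be at least as precise for the same question. With equal SDs the loss is 5% (rho 0.9) to 54% (rho 0.3) in patient numbers. At rho 0.7 to 0.5 it is 3 to 15% if the endpoint SD is 1.2 times the baseline SD, and 59 to 75% if it is 0.8 times. The direction is certain; the size rests on a correlation and an SD ratio that the article does not give, and these may differ between PANSS and the cognitive score. The variance formulas assume complete data.

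**What to change.** For both primary outcomes, replace the arm-specific baseline means with a constrained longitudinal model: baseline stays in the response vector, the two arms share one baseline mean, time has main effects, and group-by-time terms enter only at post-baseline visits. Name the treatment difference at the final visit (week 8 for symptoms, week 7 for neurocognition) as the primary contrast. With a common baseline mean this is also the difference in change from baseline, so the estimand is unchanged.

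A close alternative is to model post-baseline visits only, with the baseline value as a covariate and a baseline-by-time interaction. The two are not identical when data are missing, and 20% dropout is expected, so the plan should commit to one before unblinding.

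The cost is a change of analysis wording and at most a degree of freedom or two. The baseline values are already collected.

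### Adverse events are to be compared between arms with paired tests (McNemar, Wilcoxon signed-rank), which are not defined for this unpaired parallel-group trial

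*Protocol article*

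**What the plan says.** The Data analysis section of the protocol article names two tests for adverse events. For the share of patients affected: "The proportion of subjects with adverse events will be compared between treatments using the McNemar test". For event counts: "The number of adverse events will be compared between treatments using the Wilcoxon signed-rank test". The same paragraph also plans descriptive AE summaries, overall and by treatment.

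The design is set out under Overall design. Patients are "randomly assigned in a 1:1 ratio to receive 1000 mg of cannabidiol or matching placebo". On the allocation method it says "Blocked randomization will be used with a random block size (4 or 6") and "No stratification method will be used". The Data analysis section gives "a sample size of 120 early psychosis patients (60 per group"). The article describes no crossover period, no matched pairs and no other link between a patient on cannabidiol (CBD) and a patient on placebo.

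**The concern.** As two-treatment comparisons, McNemar and the signed-rank test both work on pairs: the same patient under both treatments, or two deliberately matched patients. McNemar uses only the pairs whose members disagree, and the signed-rank test ranks within-pair differences. Here each patient receives one treatment, so neither discordant pairs nor within-pair differences exist.

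These are the only tests that the article names for AEs. An analyst following the text literally would have to invent a pairing or run the routine on a table it was not meant for. Either way, the reported p-value would not be a proper comparison of CBD with placebo.

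**Working it through.** **Is there any pairing in the design?** Four possible sources were checked.

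- Crossover: none; each patient gets CBD or placebo.
- Matching or strata: none; stratification is expressly ruled out.
- Randomisation blocks: sizes 4 and 6 at 1:1 hold 2 or 3 patients per arm, so a block does not identify pairs.
- Before v after within a patient: both sentences compare treatments, and no patient has both.

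The tests could therefore be run in only two ways. The article gives no expected AE rate for this trial and no significance level for the AE tests. All AE rates below, and the nominal 5% level, are assumptions for illustration.

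**Route 1: pair CBD and placebo patients arbitrarily.** Assume 25/60 patients with an AE on CBD and 14/60 on placebo. Let k be the number of pairs in which both members have an AE; k can be anything from 0 to 14. The discordant counts are b = 25 − k and c = 14 − k. So b − c = 11 whatever the pairing, but b + c = 39 − 2k changes with it. Exact McNemar is a two-sided binomial test of c out of b + c at one half:

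| k | b | c | exact p |
|---|---|---|---|
| 0 | 25 | 14 | 0.108 |
| 6 | 19 | 8 | 0.052 |
| 7 | 18 | 7 | 0.043 |
| 14 | 11 | 0 | 0.001 |

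Over 20,000 random pairings of these same data, 34% gave p below 0.05. The independent-sample tests each give one value: Fisher's exact p = 0.051, Pearson chi-square p = 0.032.

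The signed-rank test behaves likewise. On one simulated set of AE counts (means 0.82 and 0.48, 60 per arm), 2,000 random pairings gave p from 0.023 to 0.235; Mann-Whitney gave the single value 0.125.

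Error rates, from 20,000 simulated trials with 60 per arm and pairing blind to outcome:

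| True AE rates | McNemar, arbitrary pairs | Independent chi-square |
|---|---|---|
| 30% v 30% (null) | 5.4% | 5.3% |
| 45% v 20% | 84.6% | 84.8% |
| 45% v 25% | 63.7% | 63.8% |

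On this route neither type I error nor power suffers materially. The fault is that the p-value is arbitrary. If the analysed arms also differ in size, for example after dropout, the surplus patients in the larger arm have no partner.

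**Route 2: run McNemar on the treatment-by-AE table.** Let x and y be the numbers of patients with an AE on CBD and placebo. The off-diagonal cells are b = 60 − x (CBD, no AE) and c = y (placebo, AE), and the statistic is (b − c)²/(b + c). Its numerator is (60 − x − y)², which depends on the total number of patients with an AE and not on the difference between arms. It tests whether the overall AE rate equals the 50% allocated to CBD. With 35% in both arms (21/60 each), b = 39 and c = 21, so chi-square = 18²/60 = 5.40 and p = 0.020 although the arms are identical. Simulated rejection at nominal 5% with equal arms:

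| AE rate in both arms | Rejection |
|---|---|
| 20% | 100% |
| 35% | 70% |
| 40% | 28% |
| 45% | 5% |
| 50% | about 1% |

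**The case against.** A reader might infer from Route 2 that the planned safety tests will produce false positives most of the time. The document does not support that. The 70% and 100% figures arise only if the treatment-by-AE table is fed to McNemar, which the article never says will be done, and the rate falls to about 1% at a 50% AE rate. Under arbitrary pairing blind to outcome, type I error holds at about 5%. Claims of inflated error should therefore be confined to that hypothetical misuse.

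It is also fair to say that little hangs on these two p-values. The primary outcomes are symptoms and neurocognition, analysed by mixed models. AE summaries by treatment remain valid and would show an imbalance. Serious-event reporting and the safety board's review do not use these tests. All of this stands and limits the consequence.

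One might add that a full protocol or SAP could name other tests. It could, but this is not a detail that the article leaves out: it names two specific tests, and both are wrong for the design it describes. The more likely explanation is a slip for the unpaired counterparts, which makes correction easy but does not make the text right.

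**Conclusion.** The point holds: the two named AE tests require pairs that this design cannot produce, so they are not defined here. This conclusion rests on the article's own description of the design and needs no assumption about AE rates.

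The size of the effect does rest on assumed rates. With arbitrary pairing the error rate is about right, but one data set can give an exact McNemar p anywhere from 0.001 to 0.108 (25/60 v 14/60), against a single Fisher p of 0.051. With the treatment-by-AE table the test answers a different question, and its false-positive rate runs from 100% at a 20% AE rate through 70% at 35% to about 1% at 50%. The damage is confined to two supporting safety p-values in this article.

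**What to change.** In the Data analysis section, replace McNemar with Fisher's exact test (or the chi-square test) for the proportion of patients with AEs. Replace the Wilcoxon signed-rank test with the Wilcoxon rank-sum (Mann-Whitney) test for the number of AEs. A risk difference with its 95% confidence interval would be a useful but optional addition. If a separate analysis plan repeats the paired tests, make the same change there. The cost is a wording change, best made before unblinded analysis; it needs no extra patients, visits or data.
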